## Abstract

**Background:**

Anorexia nervosa (AN) is characterized by dysfunctional cognitions including cognitive biases at various levels of information processing. However, less is known about the specificity of these biases, i.e., if they occur for eating-disorder-related information alone or also for non-eating-disorder-related emotional information in AN patients (content-specificity) and if they are unique to individuals with AN or are also shown by individuals with other mental disorders (disorder-specificity).

**Methods:**

The present study systematically assesses cognitive biases in 12–18-year-old female adolescents with AN on three levels of information processing (attention, interpretation, and memory) and with regard to two types of information content (eating-disorder-related, i.e., stimuli related to body weight and shape, and non-eating-disorder-related). To address not only content- but also disorder-specificity, adolescents with AN will be compared not only to a healthy control group but also to a clinical control group (adolescents with major depression or particular anxiety disorders). Cognitive biases are assessed within a single experimental paradigm based on the Scrambled Sentences Task. During the task eye movements are recorded in order to assess attention biases while interpretation biases are derived from the behavioural outcome. An incidental free recall test afterwards assesses memory biases. We expect adolescents with AN to show more pronounced negative cognitive biases on all three levels of information processing and for both types of content compared to healthy adolescents. In addition, we expect the specificity of biases to translate into differential results for the two types of content: AN patients are expected to show stronger biases for disorder-related stimuli but similar or less pronounced biases for non-disorder-related stimuli compared to the clinical control group.

**Discussion:**

This is the first study to comprehensively assess cognitive biases in adolescents with AN. It will have essential implications not only for cognitive-behavioural models of AN but also for subsequent studies aiming to modify cognitive biases in this population, thereby addressing important maintaining factors already at an early stage of the disorder.

## Background

Anorexia nervosa (AN) is a mental disorder characterized by significantly low body weight, intense fear of gaining weight and body image disturbance [1]. The disorder primarily affects adolescent girls and women with a lifetime prevalence of between 0.9% and 2.2% [2, 3]. Onset of the disorder is often in adolescence and young adulthood: roughly 40% of patients are 15–19 years old [3]. AN is a severe and highly debilitating disorder, with the highest mortality rate of all mental disorders [4, 5] and a relatively poor long-term prognosis: less than half of patients recover completely and about 20% of cases take a chronic course [6, 7].

In addition to the core symptoms, patients with AN often show dysfunctional cognitions regarding disorder-related information, i.e., information related to food, body, and weight [e.g., 8–10]. These dysfunctional cognitions manifest themselves, for example, as cognitive biases at different levels of information processing: attention to, interpretation of, and memory for eating disorder (ED)-related information. Attention biases are defined as tendencies to focus attention on information that is consistent with one’s dysfunctional cognitions [e.g., 11]. For example, to attend more to one’s unattractive body parts rather than the garment itself when trying on a new dress. Negative interpretation biases are tendencies to attribute negative rather than neutral or positive meanings to ambiguous information [e.g., 12]. For example, interpreting the shop assistant’s suggestion to try on another dress as “you’re too fat for that dress” instead of “another colour might suit you better”. Memory biases, in turn, refer to tendencies to remember information consistent with one’s dysfunctional cognitions better than other information [e.g., 13], e.g., remembering situations in which someone said something negative about one’s weight or shape better than situations in which one received a compliment. These cognitive biases are not only correlates of the disorder but are considered to play an important role in both the development and maintenance of AN [e.g., 8–11].

Empirical studies have been conducted to examine disorder-specific cognitive biases in AN, mostly focusing on attention biases for different kinds of ED-related information. A well-established finding in patients with AN is that they show attention biases for images or words related to food and eating [see e.g., 11, 14–17, for reviews and meta-analyses] as well as for stimuli related to body weight and shape [see e.g., 11, 15–17]. Interpretation biases have been less frequently examined in AN. Using an Ambiguous Scenarios Task, a negative body-related interpretation bias has been found in patients with AN [18] as well as in a broader ED sample [19]. Similarly, Brockmeyer et al. [12] found a more pronounced negative body-related interpretation bias in patients with AN compared to healthy controls using a Scrambled Sentences Task (SST). There are also only few studies on memory biases in AN. One study found patients with AN to show an explicit but no implicit memory bias for ED-related words [13] whereas another reported evidence of an implicit but no explicit memory bias [20]. Tekcan et al. [21], on the other hand, found a memory bias in AN patients in the form of hampered forgetting of ED-related words.

In addition to these cognitive biases for ED-related information, it has more recently been suggested that individuals with AN also show cognitive biases for non-ED-related emotional information, as for example emotional faces, words, or situations. Studies investigating attention biases for non-ED-related emotional information in AN have produced mixed findings: While some found stronger attention biases *towards* faces showing negative emotions in AN patients compared to healthy controls [22–24], others found AN patients to turn their attention *away* from negative faces [25] or did not find differences in attention biases for emotional faces [26, 27] or words [28] between AN patients and healthy participants. A study that investigated non-ED-related interpretation biases in AN [29] found AN patients to interpret ambiguous social situations more negatively than the control group, i.e., to show a non-ED-specific negative interpretation bias. These more general, non-ED-specific negative biases are similar to those found in individuals suffering from other mental disorders as depression and anxiety [e.g., 30]. Their presence in individuals with AN conflicts with the hypothesis that ED patients are characterized particularly by content-specific, i.e., ED-related, cognitive biases [10]. However, to properly address the content-specificity hypothesis it is necessary to assess biases for both ED-related and non-ED-related information within one study instead of examining biases for the different types of content independently. Only few studies have done so: two studies of attention biases in patients with AN and other EDs that used both ED-related and non-ED-related words found biases only for the ED-related words [31, 32]. Similarly, Williamson et al. found interpretation biases only for ED-related but not for non-ED-related ambiguous situations [19] and Hermans et al. found memory biases only for ED-related but not for non-ED-related negative words in AN patients [13].

In summary, there remains a lot to be known about cognitive biases in AN. There is evidence of biases for ED-related information on all three levels of information processing and, with regard to attention and interpretation biases, also for non-ED related information. However, particularly regarding interpretation and memory biases, evidence is rather scarce and the comparability of the studies and aggregation of their results is limited due to the use of different methods and different types of stimuli for measuring biases. The content-specificity hypothesis [10] has rarely been addressed [13, 19, 31–33]. Furthermore, no study has examined biases on all three levels of information processing within the same population. The systematic examination of cognitive biases at different levels of information processing and for both types of content is important for making systematic statements not only regarding the presence but also the magnitude and specificity of cognitive biases in patients with AN.

An additional limitation of the previous literature is that most studies on cognitive biases in AN have been performed in adult populations. Regarding interpretation and memory biases, no studies to date have compared adolescents with AN to healthy adolescents.^1^ However, the transfer of results on cognitive biases obtained in studies on adults to adolescents is problematic as major cognitive and affective development is ongoing during adolescence [35–37]. Therefore, dysfunctional cognitions might either play a smaller role in adolescent than adult AN as cognitive patterns might not have evolved into stable, trait-like “cognitive styles” yet [as suggested for depression, e.g., 38]. Alternatively, young people might be particularly susceptible to negative cues in ambiguous emotional information due to brain maturation and hormonal changes associated with an enhanced emotional sensitivity [see e.g., 39], resulting in more pronounced cognitive biases. Considering also that the incidence of AN is highest during adolescence [e.g., 3], it is particularly relevant to investigate which dysfunctional cognitions are already present at this relatively early stage of the disorder. Cognitive biases are not only suggested to be involved in the development and maintenance of AN [e.g., 8, 9], but can also be experimentally manipulated in adults [e.g., 40–43] as well as adolescents [e.g., 34] with AN or other EDs. Therefore, knowledge about cognitive biases in adolescents with AN may help to develop interventions that step in early in the course of the illness, change underlying cognitive vulnerabilities before the illness takes a chronic course, and optimize existing therapies. Therefore, the aim of the present study is to systematically investigate whether adolescents with AN show cognitive biases in attention, interpretation, and memory and to examine to what extent these biases are specific for ED-related information and to what extent they are general negative biases (content-specificity).

When studying cognitive biases in adolescents with AN it should be taken into account that a high proportion [between 47 and 60%; 44, 45] of patients also suffer from comorbid mental disorders, especially depression and anxiety disorders [e.g., 44, 46]. Both depression [47, 48] and anxiety disorders [47] are associated with negative cognitive biases in adolescents, so the presence of negative biases for non-ED-related information in adolescents with AN might be explained by their comorbidities. On the other hand, negative biases for body-related stimuli may not be specific to patients with EDs, but may be an indicator of poor self-esteem which can be found transdiagnostically in various disorders [49]. In order to investigate to what extent biases are specific to individuals with AN (disorder-specificity), AN patients are not only compared with a healthy control group (HC group) but also with a clinical control group (CC group) consisting of patients with major depression or particular anxiety disorders.

The present study assesses attention, interpretation, and memory biases within a single experimental paradigm [see 50] based on the SST [51]. The SST was initially designed as a paper–pencil test to assess depression-specific interpretation biases [51] but was converted and extended by Everaert et al. [50] into a computerized paradigm including eye-tracking that allows additional assessment of attention and memory biases. Participants have to form sentences out of arrays of words. In each trial, there is a positive and negative target word that can be used to build a positive or a negative sentence. Attention biases are derived from dwell times on negative vs. positive target words assessed via eye-tracking while interpretation biases are derived from the behavioural outcome, i.e., the number of negatively versus positively resolved sentences. Memory biases are measured via free recall of the sentences at the end of the experimental session. Thus, within the same task, i.e., using the same stimulus material, biases on all three levels of information processing can be assessed. As both positive and negative information are included within each trial, the SST measures biases for negative versus positive information, i.e., relative biases. The SST has already been used to assess depression-related biases in adolescent samples [e.g., 52–55] and found to be a valid and reliable measure, particularly for the assessment of interpretation biases [split-half reliability acceptable to excellent; 54, 55]. It assesses automatic and implicit aspects of attention, interpretation, and memory biases [e.g., 54], thereby being less susceptible to problems typical for self-report measures that allow answers to be influenced by demand characteristics, social desirability, response biases, or deliberate response strategies [e.g. 56, 57]. Biases for ED-related information and biases for non-ED-related information are assessed with different types of stimuli within the SST. Stimuli related to one’s body, weight, and shape are used to assess ED-related cognitive biases. We focus on body-related instead of food- or eating- related stimuli as implicit measures using body stimuli were found to better discriminate between females with and without eating disorders than measures using food stimuli [58]. Stimuli related to social rejection or non-body- or -appearance-related self-devaluation are used to assess non-ED-related cognitive biases. These types of stimuli have frequently been used in studies assessing cognitive biases in depression and anxiety [see, e.g., 59–61] and also by some of the above mentioned studies investigating biases for non-ED-related information in AN [22, 29].^2^ Thus, within the same task biases on all three levels of information processing and across both types of content are systematically assessed, resulting in a 3 × 2 matrix of biases.

In line with findings in adult AN patients it is hypothesized that adolescents with AN will show more pronounced negative cognitive biases compared to healthy adolescents (HC group) for both ED-related information (hypothesis 1a) [e.g., 11, 12, 20] and non-ED-related information (hypothesis 2a) [e.g., 22, 29]. Furthermore, it is expected that adolescents with AN will show stronger biases for ED-related information than adolescents with depression or anxiety disorders (hypothesis 1b), whereas biases for non-ED-related stimuli will be similar or less pronounced in adolescents with AN compared to adolescents with depression or anxiety disorders (hypothesis 2b). Adolescents with depression or anxiety disorders (CC group) are not expected to differ from the HC group regarding ED-related biases (hypothesis 1c) but to show more pronounced negative biases for non-ED-related information than the HC group as well (hypothesis 2c) [in line with e.g., 47, 48]. In summary, for ED-related biases we expect the following pattern: AN > CC = HC (hypothesis 1) and for non-ED-related biases we expect: CC ≥ AN > HC (hypothesis 2). Thus, we expect specificity of biases to translate into differential results for the two types of content (i.e., Group × Content interactions in the analyses). In addition, we will explore to what extent cognitive biases are associated with participants’ psychopathology.

## Methods

This is an experimental cross-sectional study comparing adolescents with AN to a HC group as well as a CC group on measures of ED-specific and non-ED-specific cognitive biases. The study has received ethical approval by the ethics committee of the Medical Faculty of the LMU Munich (Project-No. 20-480). Written informed consent is obtained from all participants and—for participants younger than 18 years—also from their parents/legal guardians after a comprehensive explanation of the procedures.

### Participants

A total of 105 girls aged 12–18 years will be included in the study: 35 patients with AN, 35 clinical controls (patients suffering from a depressive episode or an anxiety disorder; CC group) and 35 healthy controls (HC group). Due to the gender imbalance with significantly higher prevalence of AN in women than in men [gender ratio female:male approximately 10:1; e.g., 3], only female adolescents are included. Participants are included in the AN group if they meet diagnostic criteria for AN according to DSM-5 [1]. Participants are included in the CC group if they meet criteria for major depression, social phobia, or generalized anxiety disorder according to DSM-5 [as these are the most frequent comorbidities of AN; e.g., 44, 46; and at the same time known to be associated with cognitive biases; e.g., 47] and do not meet criteria for an ED currently or in the past. Participants are included in the HC group if they do not meet criteria for any current or past mental disorder (axis 1 disorders as assessed with a standardized diagnostic interview, see below). Exclusion criteria for all groups are: below average intelligence [IQ < 85; assessed with the CFT 20-R; 62], insufficient German language skills, non-corrected visual impairment, pervasive developmental disorders, psychotic disorders, bipolar disorder, or substance abuse.

#### Sample size

As research on cognitive biases in adolescents with AN is very scarce we had to rely on results in adult AN samples for our sample size calculation [via G*Power; 63]. The aim of the present study is to investigate whether adolescents with AN show attention, interpretation, and memory biases. With regard to attention biases for ED-related information (i.e., body-related stimuli), a meta-analysis [15] reported a medium-sized effect (Glass' *g* = 0.5) for the group difference between patients with AN and HCs. Regarding attention biases for non-ED-related information, studies reported small [*d* ≤ 0.3; 26–28, 31, 32] to large [*d* ≥ 1.1; 23, 24] effects. With respect to interpretation biases, large effects (*d* ≥ 1.5) were reported for ED-specific [12, 18] as well as non-ED-specific biases [29]. A large effect was also reported for ED-specific memory biases [*d* = 0.8; 21]. In order to detect medium to large (*η*_*p*_^2^ = 0.08)^3^ main effects of the factor Group with an α of 0.05 and a power of 0.80 in a multi-factorial analysis of variance (ANOVA) with three groups, a sample size of *N* = 87 subjects is required. Furthermore, we want to examine to what extent these cognitive biases are specific for ED-related information and expect specificity of biases to translate as Group × Content interactions in the multi-factorial ANOVAs. None of the previous studies reported an effect size for such an interaction. If a small to medium-sized effect is assumed (*η*_*p*_^2^ = 0.03), a sample size of *N* = 81 subjects is necessary to detect the interaction. Since effects might be smaller in adolescent patients and experience shows that some subjects will have to be excluded from the analysis due to insufficient data quality in the experimental paradigms that we apply (see below for criteria), we aim for a total sample size of at least 105 subjects, *n* = 35 per group to ensure sufficient power.

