#### Analyses of hypotheses

Statistical analysis of the data will be performed using IBM SPSS Statistics. Group differences in demographic and clinical characteristics (age, IQ, body-mass-index as well as ED, depression, and anxiety symptoms) and other questionnaire scores (self-esteem, body dissatisfaction, and social appearance anxiety) will be examined using univariate ANOVAs with the between-subjects factor Group (3: AN, CC, HC) and follow-up *t*-tests. The hypotheses will be addressed with separate analyses for attention, interpretation, and memory biases. Repeated-measures ANOVAs on bias scores will be performed with within-subject factor Content (2: EDR, NED) and between-subjects factor Group (3: AN, CC, HC). Significant main effects and interactions will be followed up by post-hoc ANOVAs and *t*-tests. We expect our hypotheses (hypothesis 1 regarding ED-related biases: AN > CC = HC; hypothesis 2 regarding non-ED-related biases: CC ≥ AN > HC) to translate as Group × Content interactions in the ANOVAs and corresponding results in the post-hoc tests. Associations between bias scores and psychopathology (questionnaire measures) will be assessed via Pearson’s correlations. For all analyses, the significance level will be set to *p* = 0.05 (two-tailed) and adjusted according to the Bonferroni–Holm procedure [85] when multiple post-hoc comparisons are performed. Effect sizes will be reported for all significant effects: *η*_*p*_^2^ and *η*_*G*_^2^ for ANOVA effects and Cohen’s *d*_*s*_ for between-group *t*-tests, as suggested by Lakens [86]. In addition to testing our hypotheses, we will explore to what extent cognitive biases are related to participants’ psychopathology by calculating correlations between bias scores and ED, depression, and anxiety symptoms as well self-esteem, body dissatisfaction, and social appearance anxiety.

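### The 80% power figures belong to omnibus ANOVA tests; no power is given for the pairwise t-tests that decide the directional hypotheses, and for ED-related attention bias (hypothesis 1a) it is about 38–54% at the cited effect

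*Protocol article*

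**What the plan says.** All references are to the protocol article.

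- **Sample size**, effect and test: the study is sized, at ηp² = 0.08, for "main effects of the factor Group with an α of 0.05 and a power of 0.80 in a multi-factorial analysis of variance (ANOVA) with three" study groups, giving N = 87. A second calculation, for the Group × Content interaction at ηp² = 0.03, gives N = 81. The total is raised to 105 because adolescent effects may be smaller and some data will be unusable. The result is described as "35 per group to ensure sufficient power".
- **Sample size**, evidence: for ED-related attention the cited effect is Glass' g = "0.5) for the group difference between patients with AN and HCs". For non-ED-related attention the cited effects run from d ≤ 0.3 to d ≥ 1.1. For interpretation they are d ≥ 1.5, and for ED-related memory d = 0.8.
- **Background**, hypotheses: these are stated group by group within one content, for example that "adolescents with AN will show stronger biases for ED-related information than adolescents with depression or anxiety disorders (hypothesis 1b").
- **Analyses of hypotheses**: attention, interpretation and memory are analysed separately, each by a Group × Content ANOVA. Significant effects are followed by further ANOVAs and t-tests. On the error level, "the significance level will be set to *p* = 0.05 (two-tailed") and is "adjusted according to the Bonferroni–Holm procedure [85] when multiple post-hoc comparisons are performed".

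**The concern.** A significant Group effect or interaction says that some difference exists among three groups or across two contents. It does not say that AN exceeds HC, or that AN exceeds CC, on ED-related material. Those statements come from the pairwise tests, which use two groups out of three, one content out of two, and an adjusted significance level. A study with 80% power for the omnibus test can have much less for them.

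Attention is the exposed outcome. It is analysed on its own, so the larger effects cited for interpretation and memory cannot help it, and the eye-tracking exclusions apply to it alone. The Discussion expects these results to guide the choice of biases for later intervention studies. A non-significant attention result, published beside an unqualified statement of sufficient power, could count against attention bias when the study could not settle the question.

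**Working it through.** **Inputs from the article.** α = 0.05 two-tailed; ηp² = 0.08 and 0.03; 35 per group; g = 0.5 for AN versus HC on ED-related attention; d = 0.8 for ED-related memory.

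**Assumptions, not in the article.** Correlation r = 0.5 between the two contents; a Holm family of three group comparisons per content; 29 per group (N = 87) as an illustration of losses, since no exclusion rate is given.

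**1. Reproducing the plan's figures.** With f² = ηp²/(1 − ηp²), m = 2 measurements and df = 2 and N − 3:
- Group: f² = 0.08/0.92 = 0.0870; λ = f²·N·m/(1 + (m − 1)r) = 0.0870 × 87 × 2/1.5 = 10.09; power 80.4%.
- Interaction: f² = 0.03/0.97 = 0.0309; λ = f²·N·m/(1 − r) = 0.0309 × 81 × 2/0.5 = 10.02; power 80.0%.

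Both totals reproduce. At N = 105 the powers are 88% and 90%. The 80% therefore refers to the omnibus tests.

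**2. The planned effect against the cited attention effect.** With three groups, the largest gap that corresponds to f = 0.295 is f·√4.5 = 0.63 SD (one group apart) to f·√6 = 0.72 SD (evenly spaced). In reverse, a largest gap of 0.5 SD on a single score gives f² = 0.25/4.5 to 0.25/6, so ηp² = 0.053 to 0.040. The planning value is larger than the ED-related attention effect that the section cites.

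**3. Pairwise power.** Noncentral t, df = 2n − 2, noncentrality d·√(n/2); for d = 0.5 and n = 35 this is 0.5 × √17.5 = 2.09.

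| d | n per group | α = 0.05 | α = 0.025 | α = 0.0167 (first Holm step) |
|---|---|---|---|---|
| 0.5 | 35 | 54% | 42% | 37% |
| 0.5 | 29 | 47% | 35% | 30% |
| 0.63 | 35 | 73% | 63% | 57% |
| 0.8 | 35 | 91% | 85% | 81% |
| 0.8 | 29 | 85% | 77% | 72% |

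The smallest d with 80% power at n = 35 is 0.68 unadjusted and 0.79 at the first Holm step. At d = 1.5 power is about 100%.

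**4. The whole planned sequence.** Simulated as a significant omnibus effect, then the Group ANOVA within the content, then Holm t-tests. Assumed means in SD units for AN/CC/HC are d/0/0 on ED-related and d/d/0 on non-ED-related material. The last two columns replace Holm by unadjusted pairs after a significant within-content ANOVA.

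| d | n per group | 1a, Holm | 1a and 1b, Holm | 1a, gated | 1a and 1b, gated |
|---|---|---|---|---|---|
| 0.5 | 35 | 38% | 26% | 45% | 36% |
| 0.63 | 35 | 60% | 47% | 67% | 59% |
| 0.8 | 35 | 84% | 76% | 89% | 85% |
| 0.8 | 29 | 75% | 65% | 82% | 75% |

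**5. The omnibus tests under the same 0.5 pattern.**
- Group: content-averaged means 0.5, 0.25, 0 with variance 0.75, so f² = 0.0417/0.75 = 0.0556.
- Interaction: content differences 0, −0.5, 0 with variance 1, so f² = 0.0556/1 = 0.0556.
- Either way λ = 105 × 0.0556 = 5.83, and each test has about 56% power.

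At least one of the two is significant in about 80% of runs, yet 1a is supported in only 38%.

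**The case against.** **The interaction is a stated test of specificity.** The article says several times that the hypotheses should appear as a Group × Content interaction, and on its own assumption that test has about 90% power at N = 105. This stands as far as it goes. But the article also requires matching post-hoc results, and an interaction cannot by itself show which group exceeds which.

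**The sample-size arithmetic might be thought wrong.** A reader might infer this from the gap in power. It is not: 87 and 81 both reproduce.

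**The planning effect might be thought mis-transferred from g = 0.5.** The article does not say that 0.08 derives from that figure, and the footnote attached to 0.08 is not shown. All that can be said is that 0.08 implies a larger gap than the one cited for ED-related attention.

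**The low power might be read as applying to all four directional hypotheses.** The value 0.5 is cited only for 1a on attention. For 2a on attention the cited range is wide, and for 1b and 2c no effect size is given. The joint figure for 1a and 1b therefore rests on an assumed AN–CC gap.

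**Memory might be thought safe.** At the cited d = 0.8 and 35 per group the single AN–HC comparison has 81–91%. With 29 per group it falls to 75% in the planned sequence, and to 65% jointly with 1b. No effect is cited for non-ED-related memory.

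**Holm is a valid method, and the article does not say that a null result would be read as absence of bias.** Both are true. Holm is criticised here only for spending power that three groups do not require. The misreading is a risk left open by the unqualified sufficiency statement, not something the article announces.

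**Conclusion.** The point holds as a mismatch between the tests that were sized and the tests that decide the directional hypotheses. It is not a calculation error. At the one effect the article cites for ED-related attention, the AN–HC comparison at 35 per group has 54% power unadjusted and about 38% in the planned sequence. The joint ED-related pattern has about 26% if the AN–CC gap is also 0.5. These sequence figures assume r = 0.5, the stated mean patterns and three Holm comparisons per content. The 54% needs none of those assumptions and is an upper limit for d = 0.5. Interpretation bias is not affected at the cited effects. ED-related memory is adequate for AN versus HC at 35 per group, but not clearly so after exclusions or for the joint pattern. The statement of sufficient power should be qualified accordingly.

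**What to change.** **1. Sample size section.** Keep 87 and 81, labelled as omnibus figures. Add that, with 35 per group, a two-tailed pairwise comparison within one content has 80% power for d of about 0.68 unadjusted and 0.79 at the first Holm step. State that power for the cited ED-related attention effect of 0.5 is well below 80%, so a non-significant attention result is inconclusive. For memory, claim no more than 81–91% for AN versus HC at the cited ED-related d = 0.8 with 35 per group, and say that it is lower after exclusions and for the joint pattern.

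**2. Analyses of hypotheses section, by a dated amendment before analysis.** Replace Holm among the three group comparisons within a content by the closed procedure: if the one-way Group ANOVA for that content is significant at 0.05, test each pair at 0.05. With three groups, either all pairs are equal or at most one pair is, so familywise error within that content stays at 5% (about 5% when simulated with no group differences). If this is adopted, item 1 should quote the power of the gated procedure instead of the Holm-step figures: about 45% for 1a and 36% for 1a with 1b at d = 0.5, with the assumptions stated.

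**Cost.** No added participants or software. Item 1 is wording and makes the stated power less favourable for attention. Item 2 changes a pre-specified analysis while data collection is under way, so it must be dated and finished before the data are analysed. Its error control applies within each content, not across both.
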